### 3. STUDY OBJECTIVES

The objective of this study is to assess how FirstStepDx PLUS (and NextStepDx PLUS) testing affects the variability of clinical practice and resultant impact.

#### 3.1 Primary Endpoint

Differences in CPV diagnosis/treatment domain score post-intervention versus baseline for the intervention and control group physicians).

#### 3.2 Secondary Endpoints

- Difference in utilization of appropriate treatment including indicated versus unnecessary therapy pre- and post-intervention between intervention and control groups
- Difference in utilization of laboratory testing such as fluorescence *in situ* hybridization (FISH) analyses, global assessment, and utilization of other laboratory tests pre- and post-intervention, between intervention and control groups
- Difference in overall Clinical Performance and Value Vignettes (CPV®) scores post-intervention versus baseline between intervention and control groups

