Round 2 of data collection, or post-intervention assessment, will occur 4 weeks after the introduction of the intervention.

CPV scores will be used to compare baseline practice with practice post-intervention in the 3 different physician groups/arms.

This study will test the following hypotheses:

1. Clinical practice, specifically decisions around treatment of individuals with disorders of postnatal development including DD, ASD, and ID will vary widely among all physician types. This documentation of variation in practice will demonstrate the need for a new diagnostic service that FirstStepDx PLUS and NextStepDx PLUS would fulfill.
2. FirstStepDx PLUS and NextStepDx PLUS will improve the quality and appropriateness of care and therapeutic plans, as measured by the number of physicians that correctly act on the results of the assay.

This hypothesis will be tested through total of 9 CPVs consisting of 3 CPVs cases for each of 3 case archetypes as follows.

- Case A: Patients who are currently undiagnosed and for whom FirstStepDx PLUS or would initiate appropriate therapy
- Case B: Patients who are wrongly—or incompletely—diagnosed and for whom FirstStepDx PLUS would change therapy (i.e., terminate inappropriate or unnecessary therapy and initiate appropriate therapy)
- Case C: Patients who are undiagnosed by FirstStepDx PLUS testing and for whom NextStepDx PLUS testing would initiate appropriate therapy and/or earlier intervention will result in better outcomes

The CPVs™ will be randomly assigned to physicians for each to complete 3 CPVs™ (one from each type). Each of the CPVs™ will be scored by physicians for changes in clinical practice including treatment changes, frequency of follow up, laboratory tests and imaging studies ordered - see for scoring sheet.

|                   |                                                                                                                 |                       |
|-------------------|-----------------------------------------------------------------------------------------------------------------|-----------------------|
|                   | Clinical Study Protocol                                                                                  |                       |

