With longitudinal data we can estimate the effect of FirstStepDx PLUS testing or the sequential use of FirstStepDx PLUS and NextStepDx PLUS testing on our primary and secondary outcomes. After the round 2 data is collected, we will conduct the longitudinal analysis incorporating type of intervention, time (before versus after), and the primary predictor, the time by intervention interaction (to look for differential changes over time). This allows a difference in difference analysis comparing differences between groups before and after intervention to assess the effect of FirstStepDx PLUS testing or the sequential use of FirstStepDx PLUS and NextStepDx PLUS testing.

Primary Outcome Variable:

- Quality of care (CPV® diagnosis/treatment score)

Secondary Outcome Variables:

- Use of appropriate therapy
- Utilization counts of laboratory tests and imaging studies ordered
- Overall CPV score

We will control for all potential confounders, including:

- Age
- Gender

|                   |                                                                                                                 |                       |
|-------------------|-----------------------------------------------------------------------------------------------------------------|-----------------------|
|                   | Clinical Study Protocol                                                                                  |                       |
|                   | Title: Establishing the Clinical Utility (ECU) of First Step Dx PLUS and NextStep Dx PLUS |                       |
| Supersedes: Rev B | Document Number: Rev C                                                                                          |                       |
|                   | Effective Date: 11JUNE14                                                                                        | Page: 17 of 20 |

- Number of years since fellowship
- Awareness of FirstStepDx PLUS and/or NextStepDx PLUS
- Practice location
- Type of location (urban/suburban vs. rural)
- Number of patients seen per week and number of DD/ID patients seen per week
- Number of physicians in practice
- Single or multispecialty practice
- Practice ownership (e.g. physician-physician group, community health center, etc)

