- Avg. type of coverage of patients (Medicare, Medicaid, commercial, etc)

We will model CPV™ score as a continuous outcome variable in a multiple linear regression model, which controls for all potential confounders listed above. Our regression model is as follows, where CPV™ is the score for each physician, INTERV indicates type of intervention group and TIME indicates time period (pre and post-intervention).

$Y_{it}$  = CPVscore at time  $t$ , physician  $i$

$Y_{it} \sim Normal(\mu_{ijt}, \sigma_e^2)$

$\mu_{it} = \beta_0 + \beta_1 TIME + \beta_2 INTERV + \beta_3 TIME \times INTERV + \text{control variables}$

For binary outcome variables, for example use of biologic therapy, we will use a logistic regression model. Our regression is as follows, where INTERV indicates type of intervention group and TIME indicates time period (pre and post-intervention). For outcomes with a Poisson distribution, the distributional assumption would be changed from Bernoulli to Poisson and the link would be changed from logit to log. Otherwise, the basic modeling and analysis strategy will remain the same.

$Y_{it}$  = appropriate therapy  $t$ , physician  $i$

$p_{it}$  = probability of an outcome for time  $t$ , physician  $i$

$\text{logit}(E[Y_{it}]) = \beta_0 + \beta_1 TIME + \beta_2 INTERV + \beta_3 TIME \times INTERV + \text{control variables}$

For count outcome variables such as number of follow-up visits we will use log linear regression (i.e., using a log link in the analysis). Cluster re-sampled bootstrapping will be used to check model distributional assumptions.

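### The secondary treatment endpoint contrasts indicated with unnecessary therapy, but the analysis names a single binary outcome, so unnecessary therapy has no estimate or test of its own

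*Protocol*

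**What the plan says.** - **Endpoint.** Section 3.2, and the synopsis in the same terms, gives the first secondary endpoint as "Difference in utilization of appropriate treatment including indicated versus unnecessary therapy", compared before and after the intervention and between groups.
- **Cases.** Section 2.2 describes three case archetypes, and the vignettes "will be randomly assigned to physicians for each to complete 3 CPVs", one of each type. Case A is about starting therapy. Case B is about changing it, that is, to "terminate inappropriate or unnecessary therapy and initiate appropriate therapy". Case C is about starting therapy after the second assay.
- **Hypothesis 2.** Better care is to be judged "as measured by the number of physicians that correctly act on the results of the assay".
- **Analysis.** Section 8.2 (Longitudinal Data Analysis) lists the treatment outcome as "Use of appropriate therapy". It then states: "For binary outcome variables, for example use of biologic therapy, we will use a logistic regression model". The equation defines Y as appropriate therapy for physician i at time t, with p as the "probability of an outcome for time" t and physician i. It has terms for time, intervention, their product and control variables. It has no case index and no case term.
- **Clustering.** The only mention is "Cluster re-sampled bootstrapping will be used to check model distributional assumptions".

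**The concern.** The endpoint has two parts with opposite desired directions, and Case B needs both actions from the same physician. The analysis section has one outcome and one interaction coefficient for the pair. One coefficient cannot show whether more indicated therapy was started, whether less unnecessary therapy was given, or both.

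This matters because the synopsis sets lower cost through reduced resource use as part of the objective. A result on unnecessary therapy speaks to that directly; a result on appropriate therapy as a whole does not.

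A second gap adds to the first. The three cases call for different actions, but the model is indexed only by physician and round, and no rule says how three answers become one value. The sentence that should tie the logistic model to this endpoint instead uses biologic therapy as its example. The baseline analysis also adjusts for use of biologics. Neither matches an endpoint, hypothesis or case in this trial.

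**Working it through.** **No plan figure to reproduce.** The stated power of over 80% (75 per arm, 6-7% difference, alpha 0.05) concerns the primary score. No rate, effect or power is given for the treatment endpoint. The finding comes from setting the passages side by side, and the numbers below only illustrate its consequence under assumed rates.

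**Step 1. Endpoint against model.** Section 3.2 has two components; section 8.2 has one variable. Two codings of that variable are open:
- *Ignoring:* Y = 1 if indicated therapy is given, whatever else is given.
- *Absorbing:* Y = 1 if indicated therapy is given and unnecessary therapy is not.

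**Step 2. What each coding shows.** Assume a control arm with indicated therapy at 40% and unnecessary therapy at 30%, the two being independent, and one such pair of answers per physician. Under absorbing, P(Y = 1) = indicated × (1 − unnecessary), so the control value is 0.40 × 0.70 = 0.28. Power is for 75 against 75 after the intervention, two-sided 0.05:

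Φ[(|p1 − p2| − 1.96·SE0)/SE1], where SE0 = √(2·p̄(1 − p̄)/75) and SE1 = √([p1(1 − p1) + p2(1 − p2)]/75).

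| Indicated | Unnecessary | Absorbing Y | Power, indicated alone | Power, unnecessary alone | Power, absorbing Y |
|---|---|---|---|---|---|
| 40→60% | 30→30% | 28→42% | 69% | no change | 43% |
| 40→60% | 30→50% | 28→30% | 69% | 71% | about 5% |
| 40→40% | 30→10% | 28→36% | no change | 87% | 18% |
| 40→60% | 30→10% | 28→54% | 69% | 87% | 91% |

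Row 2 in full: 0.60 × 0.50 = 0.30; p̄ = 0.29; SE0 = 0.0741; SE1 = 0.0741; (0.02 − 0.1452)/0.0741 = −1.69; Φ = 0.045.

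Under ignoring, Y is the indicated column alone. Rows 1, 2 and 4 then give the same result, although unnecessary therapy is unchanged, up or down. Under absorbing, row 2 shows almost nothing although both components moved by 20 points. Row 4 shows that the composite does well when both parts improve.

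**Step 3. The unstated rule for three cases.** If one value per physician is wanted, the rule changes what is estimated. For a per-case rate p and independent cases, any correct = 1 − (1 − p)³, at least two = 3p²(1 − p) + p³, and all three = p³. Power is for 75 against 75:

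| Per-case rate | Any correct | At least two | All three |
|---|---|---|---|
| 20→35% | 49→73%, power 85% | 10→28%, 79% | 1→4%, 27% |
| 40→55% | 78→91%, power 57% | 35→58%, 79% | 6→17%, 50% |
| 60→75% | 94→98%, power 33% | 65→84%, 79% | 22→42%, 78% |

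These are different estimands, so the spread is not bias. It shows that the result depends on a rule the protocol does not state. A case-level comparison at 40→55% has power 89%, 77% and 62% for within-physician correlations of 0, 0.2 and 0.5. Only the first of these is on the same independence footing as the table.

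**The case against.** **The label may just be short.** Section 3.2 puts both components under appropriate treatment, and neighbouring bullets in section 8.2 are abbreviated too: the laboratory endpoint loses its named tests. Appropriate could be coded to require that no unnecessary therapy is given. This stands. A reader might infer that unnecessary therapy is never tested, and the protocol does not support that. It supports only that unnecessary therapy has no separate outcome and cannot be told apart from indicated therapy.

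**No collapse is written.** A reader might also infer that the protocol reduces three cases to a single answer. That rests on subscripts alone, and the notation is loose: the linear score model carries an undefined index j. The objection stands as far as it goes. But j is absent from the logistic model and clustering appears only as a bootstrap check, so a case-level analysis cannot be read into the text either.

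**Hypothesis 2 counts physicians.** A physician-level yes/no fits that hypothesis. This stands for Hypothesis 2, but it does not deliver the contrast in section 3.2.

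**Coding belongs in the SAP or scoring sheet.** This is partly right, since neither is at hand. But the protocol itself names the outcome variable and writes its equation, and an SAP that followed it would inherit the mismatch.

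**Reporting harm as gain depends on the coding.** This stands. Under absorbing, indicated 50→60% with unnecessary 30→45% gives 0.50 × 0.70 = 35%, then 0.60 × 0.55 = 33%, which is a fall. A rise in total treatment would count as improvement only under the ignoring coding, which the protocol does not state.

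**Conclusion.** The concern holds in a limited form. Section 3.2 defines an endpoint with two components and section 8.2 names one binary outcome for it, so the plan as written gives no separate estimate of unnecessary therapy. This is true under either coding: one hides a change in unnecessary therapy, the other merges it with indicated therapy. How three cases enter a model indexed by physician and round is also left open.

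The size cannot be fixed from the protocol. Under the assumed rates and independence above, simultaneous 20-point rises in both components appear as 28% to 30%. A 20-point fall in unnecessary therapy has 87% power on its own and 18% when merged. These figures use a single post-intervention comparison of two arms, not the planned difference in differences, and would change with other rates or with correlated answers. They do not show that the planned analysis is biased.

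This is one of three secondary endpoints and the primary score is untouched. The change should be made, but it does not threaten the trial's main result.

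**What to change.** In section 8.2 (Longitudinal Data Analysis), replace the single treatment variable with two binary outcomes scored per case:

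1. indicated therapy initiated, expected to rise;
2. unnecessary therapy ordered or continued, expected to fall.

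Model each at case level by logistic regression with the existing time-by-intervention term, a case-type term and clustering on physician. If the physician-level measure in Hypothesis 2 is kept, report it as a supporting summary and state the rule that turns three cases into one value. Delete the biologic-therapy example from section 8.2 and the biologics covariate from the Baseline Data Analysis.

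The cost is protocol and SAP wording plus one additional secondary model. Section 2.2 says each vignette is scored for treatment changes, so the responses exist per case. It does not say that unnecessary therapy is recorded separately, so the scoring sheet must be checked and, if needed, given a separate item before scoring begins.

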### 4. ELIGIBILITY CRITERIA

#### 4.1 Description of subjects

Practicing physicians will be the study subjects with the following eligibility criteria.

##### 4.1.1 Inclusion Criteria

Subjects must meet the following criteria to be enrolled in the ECU Study:

1. Provide consent to participate in the study
2. Currently practicing board-certified physician in the following specialty areas:
  - a. Pediatric neurologists
  - b. Developmental pediatricians
  - c. General pediatricians
3. Have practiced as a board-certified physician for greater than 2 but less than 30 years.
4. English-speaking
5. Community / non-academic based practice setting
6. ≥30 pediatric patients under care annually
7. Access to the internet

##### 4.1.2 Exclusion Criteria

|                   |                                                                                                                 |                       |
|-------------------|-----------------------------------------------------------------------------------------------------------------|-----------------------|
|                   | Clinical Study Protocol                                                                                  |                       |
|                   | Title: Establishing the Clinical Utility (ECU) of First Step Dx PLUS and NextStep Dx PLUS |                       |
| Supersedes: Rev B | Document Number: Rev C                                                                                          |                       |
|                   | Effective Date: 11JUNE14                                                                                        | Page: 13 of 20 |

Subjects will not be included in the ECU Study if they meet any of the following exclusion criteria:

1. Not board certified in their respective area of care
2. Academic-based practice
3. Have previously used FirstStepDx PLUS and/or NextStepDx PLUS in their care delivery
4. Have practiced as a board-certified physician for less than 2 or greater than 30 years.
5. Follow <30 pediatric patients annually
6. Non-English speaking
7. Unable to access the internet

#### 4.2 Subject Screening and Enrollment

Physicians will be screened by trained recruiters for inclusion/exclusion criteria and willingness to participate in the protocol.

Informed consent will be obtained by having physicians read the consent and provide their signature and date and time of consent. Once this is obtained, physicians will be considered enrolled into the study.

#### 4.3 Subject Withdrawal

If a participant fails to complete three CPV vignettes, they will be withdrawn from the study and replaced with another physician. Any CPVs from the withdrawn subject will be excluded from the analysis.

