**Study Design** The study uses a randomized controlled study design of pediatric neurologists and developmental pediatricians and front-line (primary care) pediatricians. Physicians will be randomly assigned to a control or one of two intervention arms.

- Pre-intervention/baseline assessment: will be done using pediatric CPV® vignettes and a physician questionnaire to both control and intervention arms.
- Intervention: 2-4 weeks after baseline introduce FirstStepDx PLUS and NextStepDx PLUS to the intervention group of doctors using a webinar format to describe the application and utilization of the two assays.

|                   |                                                                                                                 |                      |
|-------------------|-----------------------------------------------------------------------------------------------------------------|----------------------|
|                   | Clinical Study Protocol                                                                                  |                      |
|                   | Title: Establishing the Clinical Utility (ECU) of First Step Dx PLUS and NextStep Dx PLUS |                      |
| Supersedes: Rev B | Document Number: Rev C                                                                                          |                      |
|                   | Effective Date: 11JUNE14                                                                                        | Page: 7 of 20 |

Post-intervention: 4 weeks post-intervention, a second round of pediatric CPV® vignettes will be administered to both control and intervention arms. FirstStepDx PLUS results will be available to order as part of the vignettes and results will be presented as a downloadable PDF for intervention group 1; FirstStepDx PLUS and NextStepDx PLUS will be available for physicians in intervention group 2.

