**Sample Size**

The study is adequately powered to detect differences in the combined diagnosis and treatment score as measured by the CPVs®. A sample size of 75 in each arm (225 total) provides over 80% power to detect an estimated 6-7% difference in scores with alpha=0.05. Due to possible attrition, extra subjects may be enrolled to ensure that at least 225 subjects will be used in the analysis.

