##### 4.3.1 Withdrawal Criteria

Reasons for study withdrawal may include but are not limited to:

- Noncompliance with study procedures.
- Physician's right to withdraw consent at any time during the study with or without stated reason.

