### 6.2 Completion of CPVs™

Enrolled physicians will be provided a website address, user name and password to access the CPVs™. Each CPV™ is expected to take approximately 15-20 minutes. Participants will be given 7 days to complete the CPVs. If the CPVs are not completed within this time frame, the physician will be contacted and requested to complete the CPVs. Physicians will be reminded to complete the CPVs by phone calls and/or emails. If after 10 business days, they still have not completed the CPV, they will be withdrawn from the study.

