### 9.2 Protected Subject Health Information

A copy of the IRB approved informed consent may be audited. The investigator or designee **must** explain to each subject the purpose and nature of the study, the study procedures, the possible adverse effects and all other elements of consent as defined in 21CFR §50.

|                   |                                                                                                                 |                       |
|-------------------|-----------------------------------------------------------------------------------------------------------------|-----------------------|
|                   | Clinical Study Protocol                                                                                  |                       |
|                   | Title: Establishing the Clinical Utility (ECU) of First Step Dx PLUS and NextStep Dx PLUS |                       |
| Supersedes: Rev B | Document Number: Rev C                                                                                          |                       |
|                   | Effective Date: 11JUNE14                                                                                        | Page: 18 of 20 |

In accordance to individual local and national subject privacy regulations, the investigator or designee **must** explain to each subject prior to screening that for the evaluation of study results, the subject's protected information obtained during the study may be shared with Lineagen and its designees, regulatory agencies and IECs/IRBs. Lineagen will not use the subject's protected information or disclose it to a third party without applicable subject authorization. It is the investigator's or designee's responsibility to obtain a written permission to use protected information from each subject. Any data collected from a subject prior to withdrawal will not be used in the analysis of study results.

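### Physicians who do not complete their vignettes are withdrawn, replaced and excluded after randomisation, so the primary analysis compares completers; the direction and size of any bias are unknown.

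*Protocol*

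**What the plan says.** The design is randomised: "Physicians will be randomly assigned to a control or one of two intervention arms" (Study Synopsis, Study Design). The same paragraph gives the baseline "vignettes and a physician questionnaire to both control and intervention arms", and Round 2 goes to all arms 4 weeks after the intervention.

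The rules on non-completion are:

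- Section 4.3: "If a participant fails to complete three CPV vignettes, they will be withdrawn from the study and replaced with another physician", followed by "Any CPVs from the withdrawn subject will be excluded from the analysis".
- Section 6.2: "If after 10 business days, they still have not completed the CPV, they will be withdrawn from the study". This is not limited to one round.
- Section 4.3.1 lists, among possible reasons for withdrawal, "Noncompliance with study procedures".
- Section 9.2, at the end of a paragraph on privacy and permission: "Any data collected from a subject prior to withdrawal will not be used in the analysis of study results".
- Study Synopsis, Sample Size: "extra subjects may be enrolled to ensure that at least 225 subjects will be used in the analysis".

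Section 4.3.2 requires the reason for withdrawal to be documented. The protocol does not give the moment of randomisation. It does not say whether a replacement is randomised or placed in the vacated arm, or whether the three vignettes are counted per round or in total.

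**The concern.** Randomisation makes the three groups comparable only as long as the physicians analysed are those who were randomised. A rule that drops physicians for what they do afterwards, and fills the gap with others, conditions the analysis set on behaviour after assignment. Replacement keeps the count at 75 per arm and so protects power. It does not restore comparability.

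The difference in difference does not cure this. It cancels stable differences in score level between physicians, but not removal that is related to how much a physician would have changed. Engagement with emailed materials and a 20-minute webinar could well be related to that, and only Groups A and B receive them (section 2.1). The primary endpoint and its p-value rest on this comparison.

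Nor is this a detail left to a statistical analysis plan. The exclusion is mandatory protocol text, and an analysis of all randomised physicians would contradict section 4.3.

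**Working it through.** **Timing.** The synopsis describes arms at the baseline round, which suggests that randomisation comes before Round 1, but no section says so. There are two cases:

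- Randomisation before Round 1: failures in both rounds are removed after allocation.
- Randomisation after Round 1: Round 1 failures are harmless. Round 2 failures are still removed after allocation and after exposure to the intervention.

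The defect therefore exists in either case. Whether three vignettes means per round or in total does not change this, because section 6.2 triggers withdrawal in any round.

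**The plan's own figure.** The stated power is over 80% with 75 per arm, a 6-7 point difference and two-sided alpha 0.05. No SD is given, so the figure cannot be reproduced directly. The largest compatible SD of the analysed score comes from SD = difference / [(1.960 + 0.842) × √(2/75)] = difference / 0.4575:

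- 6 points: 6 / 0.4575 = 13.1
- 7 points: 7 / 0.4575 = 15.3

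**Bias of a completer comparison.** Let q be the share removed in an arm, and g the mean change of completers minus that of non-completers. The as-randomised mean is the completer mean minus q × g. The completer contrast therefore equals the as-randomised contrast plus (q_I × g_I − q_C × g_C), for an intervention arm (I) and control (C). With the same gap in both arms, the bias is g × (q_I − q_C).

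The documents give neither q nor g, so the inputs below are assumptions. A gap of 6-7 points corresponds to non-completers who would gain nothing while completers gain the target effect. A gap of 10 is a less favourable assumption.

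| Excess removal | Gap | Bias (points) | Share of target |
|---|---|---|---|
| 0 | any, equal in both arms | 0 | 0% |
| 10 percentage points | 6 | 0.10 × 6 = 0.6 | 0.6/7 = 9% to 0.6/6 = 10% |
| 10 percentage points | 10 | 0.10 × 10 = 1.0 | 1/7 = 14% to 1/6 = 17% |
| 20 percentage points | 7 | 0.20 × 7 = 1.4 | 1.4/7 = 20% to 1.4/6 = 23% |
| 20 percentage points | 10 | 0.20 × 10 = 2.0 | 2/7 = 29% to 2/6 = 33% |

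If the excess removal is in the control arm, the sign reverses.

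Equal removal can also bias the result if the gap differs by arm. Suppose 15% are removed in both arms, those removed from the intervention arm would have gained nothing, and controls have no gap. An as-randomised effect of 6.0 would then be estimated as 6.0 / 0.85 = 7.06.

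**Type I error with no true effect.** SE = SD × √(2/75), which is 2.14 for SD 13.1 and 2.50 for SD 15.3. The error rate is 1 − Φ(1.96 − b/SE) + Φ(−1.96 − b/SE), where b is the bias:

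| Bias b | SD 13.1 | SD 15.3 |
|---|---|---|
| 0 | 5.0% | 5.0% |
| 0.6 | 5.9% | 5.7% |
| 1.0 | 7.5% | 6.9% |
| 2.0 | 15.4% | 12.6% |

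**Over-enrolment in place of replacement.** For 75 completers per arm, enrol 75 / (1 − d), rounded up, where d is an assumed attrition rate. This gives 79 per arm (237 in all) at 5%, 84 (252) at 10% and 94 (282) at 20%.

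**The case against.** The mandatory triggers concern vignette completion and read the same for every arm. If removal and its link with score change are equal across arms, there is no bias. Compensation (section 5), reminders (section 6.2) and short cases should keep attrition low. These points stand, and they limit the size of the problem. Nothing in the protocol, however, would show that removal was in fact balanced.

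Several stronger readings are tempting, and the documents do not support them:

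- **The effect is overstated.** A reader might infer this from the extra burden in Groups A and B. No section makes viewing the webinar a requirement or a trigger for withdrawal; section 4.3.1 only lists noncompliance as a possible reason. Controls, who receive nothing between rounds, might drop out more.
- **Data are deleted.** The text says that they are left out of the analysis. Nothing says that they are destroyed.
- **Replacements take the vacated place in the arm.** The protocol does not say this. A replacement who is randomised afresh would be an ordinary enrolment.
- **Section 9.2 is a second general exclusion rule.** It can be read that way, but it directly follows a sentence on written permission and may cover only withdrawal of permission.

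It is also fair to say that keeping everyone in the analysis does not by itself supply the missing Round 2 scores. The remedy has to name how they are handled.

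**Conclusion.** The concern holds in this form. Sections 4.3 and 6.2 require withdrawal, replacement and exclusion of non-completers. At Round 2 this happens after randomisation, and at Round 1 as well if randomisation comes first, as the synopsis suggests. The primary difference in difference is therefore a comparison of completers.

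Bias is possible and plausible, but its direction and size cannot be known from the documents. The range of 0.6 to 2 points, or about 9% to 33% of the 6-7 point target, rests on assumed excess removal of 10 to 20 percentage points and an assumed gap of 6 to 10 points that is equal in both arms. It is zero under balanced removal with an equal gap. A larger sample would not cure the problem, whereas a change of wording before the trial starts largely would.

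**What to change.** 1. Randomise each physician only after Round 1 is complete, and allow replacement only before randomisation. The 2-4 week gap before the intervention leaves room for this.
2. After randomisation, do not replace anyone, and do not exclude anyone for lateness or noncompliance. State a closing date for Round 2. Randomise afresh any physician added later.
3. Analyse all randomised physicians in the assigned arm, using every available baseline and Round 2 vignette. Add a physician-level random effect to the longitudinal model in section 8.2, which as written has only a residual error term. State that the analysis is valid under missing at random, and keep the completer analysis as a sensitivity analysis. Exclude data only where permission to use them is withdrawn.
4. Cover attrition through the extra enrolment already allowed in the synopsis, and report attrition and its reasons by arm.

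Amend 4.3 (with 4.3.1), 6.2 and the last sentence of 9.2 to match.

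The cost is protocol wording, a short wait before randomisation, slightly more analysis work and payment for the extra physicians. The estimate may turn out smaller than among completers.
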